### Increased Protease Activity in Wounds and Wound Fluid

The levels of a number of proteases and their inhibitors have been measured in different chronic wound types. These have assessed levels of proteases within chronic wound fluid (CWF), have compared levels between acute and chronic wounds, and have compared levels between nonhealing and healing chronic wounds. Results indicate that CWF has consistently elevated levels of MMPs (MMP-1,-2,-8,-9,-13) and neutrophil elastase compared with acute wound fluid [22,26,28]. Studies have demonstrated a reduction in MMPs during healing phases of VLUs and DFUs and reduced levels of tissue inhibitors of metalloproteinases (TIMPs) in nonhealing or reduced MMP/TIMP ratios during healing [23,37]. Although the levels vary between individuals, these studies indicate an association between lower levels of MMPs and healing of VLUs and DFUs.

In addition, the elevated levels of proteases within CWF are inhibitory to the healing process within chronic wounds by degrading ECM proteins and regulators of the healing process. Therefore, reduction of protease levels in CWF has the potential to improve the healing process in these wounds.

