### Point-of-Care Testing for Protease Level

A novel point-of-care testing tool, WOUNDCHEK Protease Status (WOUNDCHEK Laboratories), has been developed to determine whether wounds have an increased total protease activity. This test indicates that the total protease activity is either elevated or not elevated based on a predetermined level. It does not give a quantitative measure of total or individual protease levels. If the predetermined levels are meaningful, the test may help to guide the usage of topical agents including growth factors and protease inhibitors. There are 2 registered, ongoing, and unpublished noncomparative studies of the WOUNDCHEK Protease Status test that started recruiting in March 2012, with estimated completions in March 2013 [66], although the results are not as yet available. The studies are designed to enter 250 patients—one study for VLU and another for DFU. Each study aims to determine whether wounds with elevated total protease levels treated with protease modulating therapies have improved clinical healing trajectories at 4 weeks, which are indicative of healing outcomes at 12 weeks. There is a need for randomized controlled trials to determine whether the use of protease inhibitors guided by WOUNDCHEK Protease Status test is accurate and sensitive as compared with using a laboratory protease level assay. If WOUNDCHEK Protease Status test demonstrates clinical utility, it could be used in routine real-time wound management practice.

Recent work in the principal investigator’s laboratory has identified a potential biomarker that with a single test can determine the state of healing of a wound. In this study, GMCSF levels in CWF were elevated in nonhealing compared with healing wounds with apparent separation between the 2 groups. Overall, 90% of nonhealing wounds had a level above an observed threshold. This biomarker test, in combination with a point-of-care protease test such as WOUNDCHEK Protease Status, would provide tools for the clinician to make informed decisions on the use of topical protease inhibitors and growth factors in real time. This would represent a major advance in current wound management and be a completely novel paradigm of therapy for VLU and DFU.

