### Hypothesis

A protease inhibitor in combination with PDGF will reduce protease levels and prevent growth factor degradation in chronic VLUs and DFUs as compared with a placebo.

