### Sample Size

One small study has assessed the levels of proteases in CWF from VLU after the application of Promogran [43]. In that study, the reduction in elastase after 5 days was approximately 80%, and the reduction in MMP-9 was approximately 45%. There are no data on the degradation of rhPDGF-BB that is applied topically to VLU or DFU. For the sample size analysis, a modest reduction in protease levels of 25% was estimated. Due to the variability of factors, an SD of 35% of the value for the control levels was used. Using a power of 80% and a 5% level of significance, the calculated sample size was 31 in each group. Due to possible nonadherence with the study and collection of samples, the number of participants to be recruited is 40 in each group.

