### Data Analysis

Data analysis will be performed on the outcome measures as follows:

The trial will meet Consolidated Standards of Reporting trials (CONSORT) requirements for reporting of randomized controlled trials. Baseline characteristics of patients in the 2 treatment groups will be reported using frequency distributions and descriptive statistics including measures of central tendency and dispersion.The changes in levels of nondegraded PDGF in CWF from the treatment and placebo treatment groups will be analyzed using repeated measures analysis of variance (ANOVA), using the wound type and treatment group as covariates.The changes in levels of proteases and endogenous growth factors in CWF from the treatment and placebo treatment groups will be analyzed using repeated measures ANOVA, with the wound type and treatment group as covariates.The percentage change in wound area after 4 weeks in the study will be assessed on an intention-to-treat basis using Student *t* test. On the basis of the percentage reduction in size at 4 weeks, the ulcers will be categorized as predicted to heal or not heal at 12 weeks. These healing predictions for the Promogran and placebo groups will be assessed by chi-squared analysis.The change in total protease status after application of the Promogran or the placebo will be assessed by chi-squared analysis.The change in healing status as determined by GMCSF biomarker after application of the Promogran or the placebo will be assessed by chi-squared analysis. Healing analysis will be performed on an intention-to-treat basis.All analysis will be completed using SPSS version 22 (IBM Corporation, Armonk, New York).

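### The chi-squared comparison of change in WOUNDCHEK protease status does not condition on status before the randomised dressing, which costs power in this secondary outcome

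*Protocol article*

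**What the plan says.** The Hypothesis section expects that "A protease inhibitor in combination with PDGF will reduce protease levels and prevent growth factor degradation in chronic VLUs and DFUs". One secondary outcome is elevated total protease activity on the WOUNDCHEK swab and how it changes with time. The swab result is binary: "This test indicates that the total protease activity is either elevated or not elevated based on a predetermined level". The Data Analysis section gives the comparison: "The change in total protease status after application of the Promogran or the placebo will be assessed by chi-squared analysis".

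No inclusion or exclusion criterion concerns protease activity, and randomisation is stratified by wound type only. The one planned subgroup analysis is by wound type. The repeated measures ANOVAs name wound type and treatment group and no baseline protease term.

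Planned Interventions describes two weeks of growth factor alone, intended to give baseline protease and growth factor data. At the first visit of each week a swab is taken before the dressing goes on. A WOUNDCHEK result from before the first randomised dressing should therefore exist for every participant who reaches that point.

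**The concern.** The hoped-for change is from elevated to not elevated, and only a wound elevated at lead-in can make it. The background section on wound fluid leads one to expect a mixture: "Although the levels vary between individuals, these studies indicate an association between lower levels of MMPs and healing of VLUs and DFUs". A plain chi-squared test on all wounds has two natural readings. It may compare end status, which carries lead-in differences as unexplained variation. Or it may compare the proportion converted, which puts wounds that stayed low in the same cell as wounds that stayed high. On either reading, wounds that could not convert shrink the difference between arms.

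At stake is what a null result on this outcome would mean. The article wants to know whether protease inhibition can be followed, and perhaps guided, by a point-of-care test. Without results by lead-in status, a flat swab comparison does not separate little conversion among elevated wounds from few wounds being elevated.

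**Working it through.** **The plan's own figure.** The Sample Size section states that "a modest reduction in protease levels of 25% was estimated" and that "an SD of 35% of the value for the control levels was used". With n = 2(z₀.₉₇₅ + z₀.₈₀)² × SD² / difference²:

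n = 2 × (1.960 + 0.842)² × 35² / 25² = 30.8, so 31 per arm.

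This agrees with the plan: "Using a power of 80% and a 5% level of significance, the calculated sample size was 31 in each group". Since "the number of participants to be recruited is 40 in each group", the allowance for loss is 1 − 31/40 = 22.5%. The calculation concerns protease level. Nothing in the plan sizes the status comparison.

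**Inputs for the status comparison.** From the plan: 31 evaluable per arm, 5% significance (taken as two-sided, which reproduces 31). Assumed, because the documents give no figure: among wounds elevated at lead-in, 20% convert on the placebo dressing and 50% on Promogran; non-elevated wounds stay so; the share elevated at lead-in, π, is varied.

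**Formula.** Power = Φ{ [ |p₁ − p₂|√n − 1.96√(2p̄(1 − p̄)) ] / √(p₁(1 − p₁) + p₂(1 − p₂)) }.

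**π = 0.5, n = 31 per arm.**

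- End status, all wounds: 0.5 × 0.8 = 0.40 v 0.5 × 0.5 = 0.25. (0.835 − 1.298)/0.654 = −0.71; power 0.24.
- Converted, all wounds: 0.5 × 0.2 = 0.10 v 0.5 × 0.5 = 0.25. (0.835 − 1.053)/0.527 = −0.41; power 0.34.
- Elevated at lead-in only: 0.20 v 0.50 with n = 15.5. (1.181 − 1.322)/0.640 = −0.22; power 0.41.

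Simulation gives 0.43 for the restricted test and 0.41 for a Cochran-Mantel-Haenszel test of end status stratified by lead-in status.

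**Other shares, same formula, 31 per arm.**

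| Elevated at lead-in | End status, all | Converted, all | Elevated only |
|---|---|---|---|
| 30% | 0.14 | 0.21 | 0.26 |
| 50% | 0.24 | 0.34 | 0.41 |
| 70% | 0.38 | 0.48 | 0.55 |
| 90% | 0.58 | 0.63 | 0.66 |
| 100% | 0.71 | 0.71 | 0.71 |

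With no loss (40 per arm, simulated), a 50% share gives 0.30, 0.44 and 0.52.

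**If non-elevated wounds can become elevated.** Suppose 10% of them do, in both arms, with π = 0.5 and n = 31.

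- End status, all wounds: 0.45 v 0.30. (0.835 − 1.342)/0.676 = −0.75; power 0.23.
- Stratified end status: mean difference (0.30 + 0)/2 = 0.15; null SE ½√((0.455 + 0.18)/15.5) = 0.101; alternative SE ½√((0.41 + 0.18)/15.5) = 0.098. (0.15 − 1.96 × 0.101)/0.098 ≈ −0.50; power 0.31.
- Converted, all wounds stays at 0.34, and elevated only at 0.41.

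Stratifying still beats unstratified end status. Against the converted count it no longer gains, because it also counts changes in the unwanted direction. Restriction to elevated wounds gains in both settings.

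**The case against.** The strongest reply is that the planned analysis is of change, and change already refers to a pre-dressing status. That stands: a reader might infer that the comparison ignores baseline altogether, and the text does not support this. What is missing is conditioning on baseline. On the reading closest to the text (converted, all wounds), the gain from restriction is only 3 to 7 points in the table for shares of 30% to 90%, and power stays below 0.70. The fix improves the test without making it well powered.

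Other stronger readings also fail:

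- **Non-elevated wounds have nothing to inhibit.** The swab splits at a cut-off, so not elevated means below it, not free of protease. Such wounds can still show a fall in level, or can become elevated.
- **The trial cannot then tell whether the dressing lowers protease.** Protease levels are a separate outcome, analysed by repeated measures ANOVA, and the sample size was built on levels.
- **All-comer entry is a fault.** One aim is to validate the swab against the laboratory assay, which needs wounds of both kinds.

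The article also describes chronic wound fluid as regularly higher in protease than acute wound fluid and admits only ulcers older than three months. Dilution may therefore be slight.

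Finally, such detail could be left to an analysis plan. But the article does name the test, and it collects the variable that a better test needs.

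**Conclusion.** The point holds as a loss of efficiency in one secondary comparison. Under the assumed 20% v 50% conversion, half the wounds elevated, no change in non-elevated wounds and 31 evaluable per arm, conditioning on lead-in status raises power from about 0.24 (end status) or 0.34 (converted) to about 0.41 to 0.43. With 90% elevated the gain is about 8 and 3 points respectively; with all elevated it is nil. The conversion rates and shares are assumptions, so the true size cannot be fixed from the documents.

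A reader might infer bias, or damage to the main result. Neither follows: randomisation protects the comparison, and the primary outcome (nondegraded PDGF) and the ANOVA on protease levels are unaffected.

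**What to change.** Keep eligibility unchanged and, before the analysis begins:

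1. Define lead-in status as the last WOUNDCHEK swab before the first randomised dressing. Randomisation takes place after the first study week, so these swabs follow allocation but precede any difference in treatment and can serve as baseline.
2. Compare end-of-treatment status between arms stratified by lead-in status, by Cochran-Mantel-Haenszel or by logistic regression adjusted for lead-in status. If no non-elevated wound becomes elevated, the lead-in coefficient in the logistic model is not finite; Cochran-Mantel-Haenszel avoids this.
3. Also report conversion among wounds elevated at lead-in, with a confidence interval. It carries the same information as the stratified analysis only if non-elevated wounds never change, so both should be shown, with the number elevated at lead-in in each arm.
4. Optionally, give a treatment-by-lead-in-status estimate with confidence interval for nondegraded PDGF and protease levels, labelled exploratory. It will be imprecise at this sample size and depends on a cut-off that the trial is itself validating.

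The cost is a change of wording. The swabs are already planned, and no visit, sample or participant is added.

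### GMCSF is measured as a level but compared between arms only as healing/nonhealing status; a level analysis should be added, though the power at stake depends on how treatment moves the marker

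*Protocol article*

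**What the plan says.** The Outcome Measures section of the protocol article defines a secondary outcome as healing or nonhealing status derived from GMCSF levels in wound fluid, with its change over time, measured by ELISA. Measurement of Outcomes at Follow-Up Visits has wound fluid collected at the first and second visits of each week. A measured level should therefore be available at many time points per participant.

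The Data Analysis section then states: "The change in healing status as determined by GMCSF biomarker after application of the Promogran or the placebo will be assessed by chi-squared analysis". No analysis of the GMCSF level is named.

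The threshold is described only in the Introduction (Point-of-Care Testing for Protease Level), from work in the principal investigator's laboratory: "Overall, 90% of nonhealing wounds had a level above an observed threshold". Its value is not given, and GMCSF is presented there as a candidate marker.

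Other measurements are treated differently in Data Analysis:

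- **Proteases and endogenous growth factors:** "The changes in levels of proteases and endogenous growth factors in CWF from the treatment and placebo treatment groups will be analyzed using repeated measures". The method is an ANOVA, and its model includes wound type and treatment group. Nondegraded PDGF gets the same method.
- **Wound area:** a t test on percentage change, and a chi-squared test on the predicted-to-heal category.
- **WOUNDCHEK status:** chi-squared. The Introduction explains that this device returns only elevated or not elevated.

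**The concern.** A chi-squared test on status treats a fall in GMCSF that stays on one side of the threshold as no change, and a small fall that crosses it as a full response. The WOUNDCHEK test has no finer scale to use. GMCSF does, and its named test leaves that information out. Wound area shows that the authors accept a full-scale analysis and a threshold analysis side by side; GMCSF has only the second.

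The study plans for about 31 evaluable participants per arm. If the dressing lowers GMCSF by a general downward shift, the status test could miss an effect that the level would show, and a null result could be read as the dressing having no effect on the marker. The outcome is secondary, so the primary conclusion on nondegraded PDGF is not affected.

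**Working it through.** **Inputs (Sample Size section).** Effect: "a modest reduction in protease levels of 25% was estimated". Variability: "an SD of 35% of the value for the control levels was used". Error rates: "Using a power of 80% and a 5% level of significance". Result: "the calculated sample size was 31 in each group", and "the number of participants to be recruited is 40 in each group". The effect and SD are protease figures. Using them for GMCSF is an assumption, because the documents give no GMCSF effect, SD or status rates.

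**Step 1: reproduce the plan's sample size.** The standardised effect is d = 25/35 = 0.714. With a two-sided 5% level (sidedness is not stated), n per group = 2 × (1.960 + 0.842)² / 0.714² = 30.8, which rounds up to 31. This agrees with the plan. Exact t-test power is 79.0% with 31 per group and 88.4% with 40.

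**Step 2: shift model.** Assume GMCSF is normal with a common SD and treatment lowers the mean by d. If a share q of controls lies above the cut, the treated share above it is Φ(Φ⁻¹(q) − d). For q = 0.90 this is Φ(1.282 − 0.714) = 0.715. Power of the uncorrected Pearson chi-squared test, by exact enumeration with 31 per group:

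| Controls above cut | Treated above cut | Status test | Loss against 79.0% |
|---|---|---|---|
| 90% | 71.5% | 46.5% | 32.5 points |
| 80% | 55.1% | 56.3% | 22.7 points |
| 64% (best-placed cut) | 36% | 62.4% | 16.6 points |
| 50% | 23.8% | 58.4% | 20.6 points |

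The loss is thus about 17 to 33 points for cuts between the best-placed one and the 90% one. With 40 per group the status test has 73.4% and 57.7% at those two cuts, a loss of 15 to 31 points against 88.4%. With a continuity correction and 31 per group it has 52.1% and 33.5%, a loss of 27 to 46 points.

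**Step 3: other effect sizes under the shift model.** Normal approximation for both tests, 31 per group, with 50%, 64% or 90% of controls above the cut:

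| d | Level | Status | Loss |
|---|---|---|---|
| 0.3 | 21.8% | 10.9% to 15.1% | 7 to 11 points |
| 0.5 | 50.3% | 24.0% to 33.8% | 17 to 26 points |
| 0.9 | 94.3% | 66.5% to 79.4% | 15 to 28 points |
| 1.2 | 99.7% | 91.4% to 95.8% | 4 to 8 points |

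**Step 4: two-state model.** The Introduction also reports an apparent separation in GMCSF between healing and nonhealing wounds. Assume instead two normal components of equal SD, a cut with 90% of the nonhealing component above it, and a treatment that changes only the share of wounds in the nonhealing state. Simulated power with 31 per group, unadjusted level t test versus chi-squared on status:

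| Nonhealing share, control to treated | Separation 2.56 SD | Separation 4 SD |
|---|---|---|
| 90% to 55% | 67% vs 67% | 81% vs 76% |
| 70% to 35% | 60% vs 63% | 71% vs 73% |
| 60% to 25% | 61% vs 63% | 73% vs 74% |
| 55% to 30% | 35% vs 37% | 43% vs 45% |

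At a separation of 5 SD the status test is 1 to 8 points lower. Across these cases it ranges from an 8-point loss to a gain of about 3 points.

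**The case against.** The strongest objection is that the shift model is not the one the protocol's own description suggests. Two apparently separated groups point towards Step 4, where status carries nearly all the information. This stands: a loss of 17 to 33 points cannot be stated as a property of this trial. The documents do not settle which model holds.

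A reader might also infer from the 90% figure that the threshold is badly placed for detecting change. The documents do not support that. The figure is the share of nonhealing wounds above the threshold, not the share of trial controls. Controls receive PDGF with compression or off-loading, and some will be healing, so fewer than 90% of them may lie above it. A high share of nonhealing wounds above the line is what a status threshold is meant to achieve.

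Third, GMCSF might already be covered by the ANOVA on endogenous growth factors, since the Introduction (Enhancing Delayed Healing) lists it among growth factors tried in venous ulcers. This is possible but not the natural reading: Secondary Aims, Outcome Measures and Data Analysis each list GMCSF separately from endogenous growth factors, and Data Analysis gives it its own test. If coverage was intended, the section should say so.

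Finally, status is the defined outcome and a clinic test is the long-term purpose, so the chi-squared comparison answers the question posed. This also stands. It rules out replacing the status test, but not adding a level analysis.

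**Conclusion.** The point holds in a limited form. Data Analysis fixes a two-state comparison for a marker measured as a level and names no level analysis for it, unlike its treatment of the other assayed wound-fluid levels and of wound area.

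The cost has no single value. It is about 17 to 33 points of power if treatment shifts a roughly normal level by the borrowed protease effect with 31 per group and the cut lies in the range described. It is close to nil if treatment moves wounds between two well-separated states. Because the documents do not say which applies, planning both analyses protects against either case. The stronger conclusion, that the status test is wrong and should be dropped or reduced to a table, does not follow, because status is the outcome as defined.

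**What to change.** In Data Analysis, add one sentence: the GMCSF level (log scale if skewed) will be compared between arms with the repeated-measures model already planned for proteases and endogenous growth factors, with wound type as covariate and the level during the gel-only lead-in as baseline. Keep the chi-squared comparison of healing status beside it, as is already done for wound area.

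The cost is one more secondary analysis to report. No new samples, assays, visits or patients are needed.

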### Frequency of Analyses

All statistical analyses will be performed only at the completion of the study and after final data checking is completed.

### Planned Subgroup Analyses

If the initial analysis demonstrates a difference between VLU and DFU responses to protease inhibitor application, subgroup analyses of these 2 groups will be performed.

### Previous Pilot Testing

There is one small study that has demonstrated reduction in elastase and MMP-9 levels in CWF from VLU with the application of Promogran [43]. There is one study that has demonstrated degradation of EGF by CWF, but none that has demonstrated degradation of PDGF in VLU or DFU [26].

### Trial Management

The study will employ a research coordinator 2 days per week to manage data handling, randomization, and other aspects of the study. A total of 2 clinical research nurses will be employed to perform the dressings and application of the study treatments.

The principal applicant will oversee, in conjunction with the research coordinator, the management of the study, the location and facilities for the study, treatment materials and data storage systems, and the analysis of the data from the study.

A study steering committee will be formed from experienced researchers within the Population Health Research Institute in Hamilton. A data and safety monitoring board will be blinded to treatment group. The board will review serious adverse events.

